#### Measures

##### Demographics and Background Information

Information collected at baseline will include age, sex and gender, race, weight and BMI, education level, medications, history of psychological symptoms, history of psychological treatment, and history of substance use and substance use treatment.

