#### Analytic Plan

We will examine the frequencies of our feasibility, adherence, and acceptability variables. Although the primary focus is on feasibility and acceptability, we also plan to examine the direction of effects on outcomes. Our primary outcome is alcohol use. We will conduct chi-square and logistic regressions for categorical outcomes, and analysis of covariance for continuous variables (controlling for baseline measurements) to examine differences in outcomes between the intervention and control groups at the postintervention evaluation. For the 6-month follow-up, logistic regression will be used for the categorical outcome (eg, any alcohol use at 30 days), and hierarchical linear modeling will be used to examine repeated measurements of alcohol use quantity and frequency, covarying for baseline levels of those variables and demographics. Hierarchical linear modeling is optimal for analyzing longitudinal data, as it allows for control over missing data and comparison of more than 2 waves of data [38,39].

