## Results

This project was funded by the National Institute on Alcohol Abuse and Alcoholism on September 20, 2020. After completing patient interviews and an open trial to refine the intervention, recruitment for the pilot randomized controlled trial began on November 8, 2023, and the final participant was enrolled on August 14, 2024. A total of 60 patients were enrolled.

Because this is a pilot trial, the primary focus will be on the feasibility of the study protocol, adherence to the intervention, and acceptability of intervention content. We anticipate having an enrollment rate of 50% and at least 75% who complete each assessment. We anticipate that at least 75% of the participants will initiate the intervention (ie, complete at least 1 CBI session). To measure adherence and engagement in the intervention content, we anticipate that at least 75% of the weekly SMS text messages will be responded to and that at least 75% of the participants will complete the intervention (ie, complete both CBI sessions and continue to receive the 3 months of SMS text messaging). We also expect that the majority (>50%) of participants will rate each of the acceptability items as positive and that at least 75% of the participants will believe that other patients would use the intervention after MBS. We have set these benchmarks, as they are deemed reasonable definitions of success for pilot trials [40].

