### Strengths and Limitations

This study has several strengths, including the preventive approach to mitigating AUD after MBS; the use of a control group as a comparison to treatment-as-usual; and the collection of data that includes feasibility, acceptability, and preliminary outcomes. However, it is important to note several limitations. First, this is a pilot study with a small sample size. Consequently, the study may not be appropriately powered to detect changes in alcohol use. Therefore, the goal is to examine the direction of the effects to determine whether a future, fully powered trial is worthwhile. Second, the length of follow-up is short; therefore, the ability to prevent the development of an AUD cannot be assessed. Finally, alcohol use is measured by self-report, and it is possible that patients may minimize their use or report their use inaccurately.

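### Drinking quantity and frequency: the 3-month and 6-month effects rest on different patients, missing-data handling and covariates, and neither model names time since surgery

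*Protocol article*

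**What the plan says.** All of this is in the protocol article.

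- **3 months (Analytic Plan).** Continuous outcomes are compared by "analysis of covariance for continuous variables (controlling for baseline measurements"), in order "to examine differences in outcomes between the intervention and control groups at the postintervention evaluation".
- **6-month follow-up (Analytic Plan).** "hierarchical linear modeling will be used to examine repeated measurements of alcohol use quantity and frequency", "covarying for baseline levels of those variables and demographics". The article justifies this model by its handling of missing data and its ability to use more than two waves.
- **Visits (Participants and Procedures).** Assessments after baseline are at 1 month, 3 months and the 6-month follow-up. Urn randomization uses sex and time since surgery.
- **Demographics (Demographics and Background Information).** The items collected include "age, sex and gender, race, weight and BMI, education level". The Analytic Plan does not say which of them enter the model.
- **Size and attendance (Results).** "A total of 60 patients were enrolled", and the benchmark is "at least 75% who complete each assessment".
- **Purpose (Strengths and Limitations).** Power is acknowledged to be limited, and "the goal is to examine the direction of the effects".

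**The concern.** Drinking days (0 to 30) and drinks per day are numerical outcomes, and no other 3-month method is named for them. The natural reading is therefore that they fall under the ANCOVA, although that sentence does not name them.

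On that reading, the 3-month effect comes from the patients who attended that visit, adjusted for baseline alone. The 6-month effect comes from everyone with at least one usable wave, adjusted for baseline and demographics, with missing visits handled through the correlation between waves. A reader who sets the two effects side by side cannot separate a change over time from a change of method.

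The 3-month result also forgoes the missing-data advantage for which the article chose the hierarchical model. In addition, time since surgery shaped the allocation, yet neither model names it.

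What is at stake is the clarity and some of the precision of secondary effect estimates that will inform whether a larger trial is worthwhile.

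**Working it through.** The article gives no effect size, standard deviation or power figure for these outcomes, so there is no stated figure to reproduce. The checks below use 60 patients and 75% attendance from the Results section. Correlations, 1:1 allocation and dropout patterns are assumptions.

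**1. The two analyses side by side**

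| | 3 months | 6-month follow-up |
|---|---|---|
| Model | ANCOVA at one visit | Hierarchical model, repeated waves |
| Patients | Seen at that visit | Any usable wave after baseline |
| Baseline value | Yes | Yes |
| Demographics | No | Yes |
| Time since surgery | Not named | Not named |
| Sex | Not named | Only if a demographic |

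With baseline as a covariate, the outcome waves are months 1, 3 and 6. More than two waves then requires month 3, so the 3-month data are already in the hierarchical model.

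**2. Patients contributing**

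- ANCOVA at 75% attendance: 60 × 0.75 = 45.
- Repeated-measures model, if attendance is independent across three visits: 60 × (1 − 0.25³) = 60 × 0.984 = 59.
- If the same 15 patients miss every visit, both models have 45. The range is therefore 45 to 59.

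**3. Gain at 3 months from the repeated-measures model**

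The comparison is by simulation: baseline-only ANCOVA against a repeated-measures model with baseline and the randomization factors, at 75% attendance and correlations of 0.6 to 0.75 between waves.

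- Missing at random by chance: the variance of the 3-month contrast is about 3-6% lower. A repeat of 4,000 trials (equal correlations, known covariance, no effect) gave standard deviations of 0.240 and 0.236 at correlation 0.6, a variance ratio of 0.968. At correlation 0.75 the ratio was 0.953.
- Month-3 attendance dependent on month-1 drinking in one arm: bias fell from −0.07 to −0.02 outcome SD. The repeat used a milder pattern (in one arm, attendance of 60% or 90% according to month-1 drinking) and gave −0.04 against 0.00 at correlation 0.6. The size depends on the assumed pattern; the direction was the same.

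**4. Do the demographics cost precision?**

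Adding k terms that do not predict the outcome, beside arm and baseline, multiplies the variance by about (n − 4)/(n − 4 − k). The interval also widens by the ratio of t quantiles.

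| n | k | Variance factor | SE factor | Interval width |
|---|---|---|---|---|
| 60 | 3 | 56/53 = 1.057 | 1.028 | +2.9% |
| 60 | 8 | 56/48 = 1.167 | 1.080 | +8.4% |
| 45 | 3 | 41/38 = 1.079 | 1.039 | +4.1% |
| 45 | 8 | 41/33 = 1.242 | 1.115 | +12.2% |

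The break-even share of residual variance explained is about k/(n − 4): 3/56 = 5% to 8/56 = 14% at n = 60, and 3/41 = 7% to 8/41 = 20% at n = 45. Above that share, the demographics narrow the interval. With n = 60 and k = 5, simulated width ratios were 1.05, 1.00 and 0.94 when they explained 0%, 10% and 20%.

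**The case against.** The strongest reply is that the plan assigns one model to each time point, so nothing is ambiguous: ANCOVA gives the 3-month result and the hierarchical model the 6-month result. A visit-specific ANCOVA followed by a longitudinal model is a legitimate design. The outcomes are secondary, the primary alcohol outcome is binary drinking status, feasibility comes first, and no decision rule rests on quantity or frequency. A full protocol or analysis plan may also list the demographics.

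Most of this stands, and it rules out two stronger readings.

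- **Two rival 3-month estimates, open to choice once the data are seen.** A reader might infer this because the 3-month wave enters both models. The article plans no 3-month contrast from the hierarchical model. Simulated estimates from the two approaches do take opposite signs in some trials with no effect, but the covariates are only part of the reason: 6-8% do so even with identical covariates, against 8-15% with 3 to 12 demographic terms.
- **Demographic adjustment wastes precision.** The working shows a small loss if the terms are useless and a gain if they are moderately prognostic. The article does not settle which holds. Sex, being a randomization factor, has a design reason to be included.

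The reply does not remove the mismatch itself. Listing the demographics would still leave the 3-month and 6-month effects on different patients, missing-data handling and covariates.

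**Conclusion.** The point holds in a limited form. For drinking quantity and frequency, the two time points are analysed on different bases, and the 3-month analysis does not use the model that the article itself prefers for missing data. Time since surgery, a randomization factor, is named in neither model.

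The benefit of changing this is modest: about 3-6% lower variance for the 3-month contrast, and less bias if attendance depends on earlier drinking. It rests on 75% attendance, correlations of 0.6-0.75 and the reading that quantity and frequency fall under the ANCOVA. With near-complete attendance the gain would be close to nil, and the main benefit would be comparability of the two time points. The validity of the trial and its primary alcohol outcome are not in question.

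**What to change.** For quantity and frequency, fit one repeated-measures model per outcome with months 1, 3 and 6, categorical time and an arm-by-time term. Use one covariate set that contains the baseline value, sex and time since surgery. Report both the 3-month and the 6-month arm contrasts from it, and say that it replaces the 3-month ANCOVA for these outcomes. The ANCOVA can remain for the other continuous measures.

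Whether further demographics stay in the model is for the trial team to weigh. Whatever is chosen should apply to both time points and be fixed before the data are examined.

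The cost is a change of analysis wording, slightly more modelling, and reliance on the repeated-measures model for the 3-month result. No data collection changes.

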## Results

This project was funded by the National Institute on Alcohol Abuse and Alcoholism on September 20, 2020. After completing patient interviews and an open trial to refine the intervention, recruitment for the pilot randomized controlled trial began on November 8, 2023, and the final participant was enrolled on August 14, 2024. A total of 60 patients were enrolled.

Because this is a pilot trial, the primary focus will be on the feasibility of the study protocol, adherence to the intervention, and acceptability of intervention content. We anticipate having an enrollment rate of 50% and at least 75% who complete each assessment. We anticipate that at least 75% of the participants will initiate the intervention (ie, complete at least 1 CBI session). To measure adherence and engagement in the intervention content, we anticipate that at least 75% of the weekly SMS text messages will be responded to and that at least 75% of the participants will complete the intervention (ie, complete both CBI sessions and continue to receive the 3 months of SMS text messaging). We also expect that the majority (>50%) of participants will rate each of the acceptability items as positive and that at least 75% of the participants will believe that other patients would use the intervention after MBS. We have set these benchmarks, as they are deemed reasonable definitions of success for pilot trials [40].

We hypothesize that those in the intervention group will have a lower proportion of individuals engaging in alcohol use at the postintervention and follow-up assessments compared to the control group. We also expect that individuals in the intervention group will report greater importance to avoid alcohol use compared to the control group at the postintervention evaluation and follow-up. Because this is a pilot study and we may not be powered to detect between-group differences, we will also explore changes within groups to determine whether there is potential for an effect (ie, a significant increase in their rating on the importance of avoiding alcohol use among the intervention group). We will explore potential differences between the intervention and control groups for our other outcomes, including proportion of individuals with hazardous drinking, attitudes toward drinking, psychiatric symptoms, and eating and lifestyle behaviors. Although we do not expect statistically significant differences given the small sample size, we hypothesize that those in the intervention group will show a direction toward improvement, and we will examine the effect sizes of the intervention.

## Discussion

### Anticipated Findings

The goal of this pilot randomized controlled trial is to examine the feasibility and acceptability of a multicomponent technology-based intervention and to examine the direction of intervention effects. We anticipate that this study protocol will be feasible, that participants will engage with and adhere to the components in the technology-based intervention, and that participants will find the intervention content acceptable. We also anticipate that those randomized to the intervention group will have lower alcohol use than those in the control group. Other technology-based interventions for reducing substance use have been feasible, acceptable, and successful at reducing substance use, so this approach will likely translate to individuals who undergo MBS [41]. However, most interventions for substance use are targeted at individuals who have developed substance abuse; therefore, this approach is unique in that the goal is preventive. Moreover, given that the risk of AUD after MBS increases between 1 and 2 years postoperatively, delivering content to the population between 3 and 18 months postoperatively could capture the most vulnerable period for reinitiation and escalation of alcohol use [4].

### Strengths and Limitations

This study has several strengths, including the preventive approach to mitigating AUD after MBS; the use of a control group as a comparison to treatment-as-usual; and the collection of data that includes feasibility, acceptability, and preliminary outcomes. However, it is important to note several limitations. First, this is a pilot study with a small sample size. Consequently, the study may not be appropriately powered to detect changes in alcohol use. Therefore, the goal is to examine the direction of the effects to determine whether a future, fully powered trial is worthwhile. Second, the length of follow-up is short; therefore, the ability to prevent the development of an AUD cannot be assessed. Finally, alcohol use is measured by self-report, and it is possible that patients may minimize their use or report their use inaccurately.

### Conclusions and Future Directions

Patients who undergo MBS are at an increased risk of developing a postoperative AUD. Previous research has suggested a need for strategies to reduce postoperative alcohol use to mitigate the risk of an AUD. A technology-based approach could be a feasible and acceptable method of delivering preventive strategies to individuals after MBS. If successful, this project will provide the necessary support to conduct a fully powered randomized controlled trial to examine its efficacy in reducing alcohol use and with longer-term follow-up to determine whether it can reduce the incidence of AUD. Consequently, the next step after this pilot study is to conduct a randomized trial of this technology-based intervention compared to a control group. We plan to determine whether this intervention could prevent the reinitiation of postoperative alcohol use and reduce alcohol use among those who did reinitiate drinking after MBS. We also plan to test mediators and moderators in future work, as well as to examine the factors necessary for the successful implementation with MBS programs. Our long-term goal in this line of research is to develop an effective program that is scalable and sustainable within MBS programs to mitigate the risk of hazardous alcohol use and AUD.

## Data Availability

Data sharing is not applicable to this paper as no datasets were generated or analyzed during this study.

## Appendix

Multimedia Appendix 1 Peer review report by AA-3 Clinical, Treatment and Health Services Research Review Subcommittee, National Institute on Alcohol Abuse and Alcoholism Initial Review Group (National Institutes of Health, USA).

## Abbreviations

AUD: alcohol use disorder
CBI: computerized brief intervention
MBS: metabolic and bariatric surgery
MI: motivational interviewing
TTM: transtheoretical model
